The MyPeBS study^2^ is an ongoing randomised controlled trial currently running in six countries (Italy, France, Israel, the UK, Belgium, and Spain) that is testing whether a risk-stratified screening strategy is non-inferior, or eventually better at reducing incidence of advanced breast cancer (i.e. cancers diagnosed at stage 2 or higher), than standard age-based screening. Women from the general population aged 40 to 70 are eligible if they live in a participating area from one of the six participating countries and have never had breast cancer or a high breast cancer risk condition. Participants are randomised 1:1 between the standard arm and the risk-based arm. In the standard arm, women are screened for breast cancer according to the current national guidelines and procedures (bi-yearly or tri-yearly mammogram and/or tomosynthesis, with ultrasound in case of dense breast, starting at age 45–50, up to age 69–74 depending on countries). For the women in the risk-based arm, screening frequency and method depend on their individual 5-year predicted risk of invasive breast cancer, which is estimated at study entry. Risk stratification is done using validated clinical risk scores including a polygenic risk score performed on DNA extracted from a saliva sample and comprising 313 relevant polymorphisms, adjusted for national breast cancer incidence [15]. The primary endpoint (incidence of stage 2 + breast cancer) is measured after four years, at the end of follow-up. Secondary endpoints include false negative and false positive findings, over diagnosis, cost-effectiveness, long-term breast cancer specific mortality, and the present patient-reported data and outcomes.

This study is relevant to address the relative impact of risk-stratified screening for several reasons. First, it is a very large study, with 85,000 women to be randomised. Second, each of the countries in the MyPeBS study have a routine screening programme in which the study is inserted, and against which any additional benefits and harms of risk-stratified screening can be readily compared. Third, it takes place across six different countries with differing screening programmes, healthcare organisations, cultures and ethnic minority populations. Given this, any comparisons of the two approaches to screening will take into account these background factors, to allow the conclusions to be generalisable across countries, or to flag up where caution is needed in making generalisations.

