### Sample size justification

The present study is embedded within the main MyPeBS trial, which aims to recruit 85,000 women from six countries, in 2.5 years, and randomise them to receive either usual screening or risk-stratified screening. The sample size for the main MyPeBS study was based on providing sufficient statistical power to detect non-inferiority of risk-stratified screening in progression of participants to stage 2 breast cancer or beyond.

The present consideration of socio-psychological aspects of risk-stratified screening in the MyPeBS trial will involve the recruitment and follow-up of the entire study sample of women in the MyPeBS trial. This will provide very high statistical power for the five main objectives of the present study. For example, as of December 31st, 2021, 22,884 participants have been recruited, and assuming 70% follow-up of the first 22,000 women, the present study will have over 99% power to detect a very small difference (standard mean difference of 0.08) between the two experimental groups.^3^ Thus, the present sample size will provide more than sufficient statistical power for the five main objectives presented in this paper, and allow well-powered comparisons of these variables in each of the six countries (the sixth objective).

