#### c. Bivariate analyses and subgroups comparisons

The bivariate analyses will mainly focus on detecting differences between subgroups (e.g., countries). Before, it will be ensured that each group contains a sufficient number of participants and is adequately powered.

For the qualitative or discrete variables, the significant differences between subgroups will be assessed either by means of the Chi-square test or by Fisher's exact test depending on the conditions of statistical validity (i.e., theoretical number strictly less than 5).

The Cochran Mantel Haentszel test (or Q Cochran) will test for equality of proportions in matched samples. It will be used to test, for instance, how the comprehension level of risk stratified screening varies in time, (i.e., between baseline, three months and four years).

For quantitative variables, significant differences between two subgroups will be detected via Analysis of Covariance (ANCOVA), controlling for baseline levels of those variables, and any other clinical or demographic variables that are not well balanced between subgroups, and hence may have a confounding effect. Initial assumption testing will include the Fischer test, which will be used to verify the hypothesis of equality of variances, and the Shapiro Wilk test, which will be used to verify the hypothesis of normality. In the case of non-normality, non-parametric approaches will be used in sensitivity analyses. In this case, the Wilcoxon or Mann–Whitney test for comparisons between two subgroups and the Kruskal–Wallis test beyond two subgroups will be considered.

The tests will be bilateral with a significance level of 5%. Adjustments for multiple comparisons (Bonferroni correction) do not appear to be required.

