According to the literature, no method for managing missing data is unanimously accepted. As a result, automatic replacement of missing data will not be used [56]. The analyses will be conducted on all patients included with no missing data. In case of no answer, we will assume that the data are missing at random. This assumption will be tested by comparing the characteristics of respondents and non-respondents using the Chi-square statistic. Another source of missing data will likely come from women not answering subsequent waves of the survey (for instance, questionnaires at one year, two years or four years). In other words, we may face an attrition issue. First, we will test whether attrition is non exogenous (i.e., data are not missing at random), which could bias our estimates from longitudinal models assessing the evolution of our main dependent variables over time. In order to test for exogenous attrition, we will compare the results from the balanced (i.e., with no missing data) and unbalanced (i.e., with missing data points) panel using an Hausman test [57]. Rejection of the null assumption of equality of coefficients between the two panels will provide evidence of non-exogenous attrition. In case non exogenous attrition is detected, we will use inverse probability weighting to correct for the selection effect, i.e., we will weight women by the inverse of their probability of selection [58]. This method has been shown to reduce the selection bias in epidemiological applications.

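### The missing-data rules test an assumption that data cannot test, reserve weighting for loss it cannot correct, and leave the baseline-adjusted arm comparison on complete cases with no clear correction

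*Protocol article*

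**What the plan says.** The rules stand in the missing-data paragraph of Appendix 1, section c.

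- **Analysis set.** Automatic replacement of missing values is ruled out, and "The analyses will be conducted on all patients included with no missing data".
- **Assumption and its test.** Non-response is assumed to be MAR, and "This assumption will be tested by comparing the characteristics of respondents and non-respondents using the Chi-square statistic".
- **Wave attrition.** The plan equates non-exogenous attrition with data that are not missing at random, and describes it as a threat to the estimates from longitudinal models. It is to be detected by a Hausman test comparing the balanced and unbalanced panels.
- **Remedy.** "In case non exogenous attrition is detected, we will use inverse probability weighting to correct for the selection effect".

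The same section sets ANCOVA, controlling for baseline, as the method for quantitative outcomes. Appendix 2 gives baseline-adjusted comparison of the arms as the analysis for anxiety and cancer worry. Section d.2 adds random-intercept mixed models over time and refers back to the attrition rules. The Sample size justification works its power example "assuming 70% follow-up of the first 22,000 women".

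**The concern.** Three rules are wrong or unclear as written.

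1. MAR concerns dependence on values nobody has seen, given what has been seen. A difference between respondents and non-respondents on observed characteristics argues against missing completely at random (MCAR) and is fully compatible with MAR. The absence of a difference does not establish MAR either.
2. Inverse probability weighting (IPW) built on observed data needs MAR given the variables in the weight model. The plan reserves it for loss it labels as not missing at random, and its trigger does not distinguish the two situations.
3. The complete-case sentence covers the analyses in general, while the Hausman and weighting step is framed around longitudinal models. Whether the weights carry into the section c ANCOVA is not said. The complete-case sentence also conflicts with the unbalanced panel in the same paragraph and with the mixed models of section d.2, and no panel is named as primary.

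The first objective asks whether risk communication causes distress, comparing change from baseline at one year. If worried women in the risk arm stop answering, complete-case ANCOVA moves towards no harm. A large sample only makes that estimate more precise.

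**Working it through.** **The plan's own figure.** Inputs: two-sided 5% tests ("The tests will be bilateral with a significance level of 5"), 1:1 allocation ("Participants are randomised 1:1 between the standard arm and the risk-based arm"), 70% of 22,000 women, and a "standard mean difference of 0.08". Women analysed: 0.70 × 22,000 = 15,400, or 7,700 per arm. Noncentrality: 0.08 × √(7,700/2) = 4.964. Power: Φ(4.964 − 1.960) = Φ(3.004) = 99.87%. The claim that "the present study will have over 99% power to detect a very small difference" reproduces. It concerns precision and says nothing about bias.

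**Size of the complete-case bias at one year.** The inputs below are assumptions, apart from the 30% loss and the 0.08 SD effect, which come from the power example:
- 11,000 women per arm and about 30% lost in each;
- unit SDs, with correlations baseline to 3 months 0.65, baseline to 1 year 0.55, and 3 months to 1 year 0.60;
- arm effect 0.15 SD at 3 months and 0.08 SD at 1 year;
- random loss in the standard arm; in the risk arm the odds of loss are multiplied by OR per SD of 3-month worry. This is MAR, because the 3-month score is observed.

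To first order, ANCOVA adjusting for baseline only has

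bias ≈ −(r(3m,1y) − r(b,3m) × r(b,1y)) × proportion lost × ln(OR)
= −(0.60 − 0.65 × 0.55) × 0.30 × ln(OR) = −0.07275 × ln(OR).

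| OR per SD | ln(OR) | Bias | Expected estimate | Simulated complete-case ANCOVA |
|---|---|---|---|---|
| 1.25 | 0.223 | −0.016 | 0.064 | 0.061 to 0.064 |
| 1.5 | 0.405 | −0.029 | 0.051 | 0.049 to 0.052 |
| 2.0 | 0.693 | −0.050 | 0.030 | 0.026 to 0.032 |

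The last column spans separate simulation runs (200 replicates where the count is recorded). IPW using the 3-month score, or a mixed model on all waves, gave 0.078 to 0.085 across these scenarios.

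The plan's own gate was also run on this scenario (150 replicates, random-intercept model). The Hausman test rejected in 100% of runs at all three ORs, and in 2% with no selective loss. The plan would therefore call for weighting here. The bias stays only where the weights are not carried into the ANCOVA.

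**Do the tests identify the mechanism?** A second simulation used 22,000 women, four waves, loss only at four years (about 70% response), true effect 0.080 and 300 replicates per scenario. Within-woman correlation 0.5 and a log-odds slope of 0.5 are assumptions. The slope is per SD of the score and in the risk arm only; in the covariate scenario it is per category and in both arms. The chi-square used one baseline characteristic.

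| Loss depends on | Chi-square rejects | Hausman rejects | Complete-case ANCOVA | IPW |
|---|---|---|---|---|
| nothing (MCAR) | 3% | 1% | 0.082 | 0.081 |
| a baseline covariate (MAR) | 100% | 2% | 0.079 | 0.079 |
| 1-year score (MAR) | 4% | 100% | 0.043 | 0.081 |
| unseen 4-year change (MNAR) | 5% | 28% | −0.007 | −0.014 |
| 4-year level (MNAR) | 5% | 100% | −0.033 | −0.016 |

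The chi-square rejects where the complete-case analysis is unbiased, and stays near its nominal level where that analysis is biased. The Hausman test rejects under MAR, where weighting works, and under one form of MNAR, where it does not. It misses the other form of MNAR in 72% of runs.

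**The case against.** The strongest reply is that the gate does its job where weighting can help. In the one-year MAR scenario, and in the four-year scenario with loss driven by the 1-year score, the Hausman test rejects every time and weighting restores the effect. This stands, and it limits the complete-case figures to an ANCOVA that the weights do not reach.

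Other points also stand. The mixed models of section d.2 can already use all available waves, so complete-case analysis is literal mainly for section c. The plan also says, more softly, that weighting reduces selection bias. The 70% follow-up is a worked example and not a forecast. The two anxiety and worry scales are not given in France, so 22,000 is not the sample for these outcomes; the bias formula does not depend on sample size. The outcomes are secondary in the parent trial.

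A reader might infer that weighting can never repair the loss the Hausman test flags, that the plan never corrects MAR attrition, or that the balanced and unbalanced panels always share the same bias. The documents do not support these readings. A rejection does not establish MNAR. Correction is planned for the longitudinal models. In the one-year MAR scenario the panels diverged: the unbalanced model gave 0.080 to 0.081, the balanced one 0.041, 0.007 and −0.037. Both panels were biased only under MNAR.

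None of this rescues the stated test of MAR, the mismatch between the remedy and the plan's own label, or the silence on the ANCOVA.

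**Conclusion.** The concern holds in this form. MAR is wrongly treated as testable from respondent characteristics. Weighting is assigned to loss that the plan calls not missing at random, through a test that does not separate MAR from MNAR. The baseline-adjusted ANCOVA rests on complete cases with no clearly stated correction, in conflict with the unbalanced panel and the mixed models, and no panel is primary.

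Under the assumed correlations and about 30% loss, the ANCOVA would report roughly 0.06 to 0.03 SD for a true 0.08 if loss in the risk arm rises with 3-month worry at OR 1.25 to 2.0 per SD. The sizes rest on assumed dropout strength; the direction follows from the assumed pattern of loss. The stated power is arithmetically right and unaffected. This should be fixed before outcomes are analysed, but it does not invalidate the study.

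**What to change.** - Drop the chi-square and Hausman tests as gatekeepers. Report respondent and non-respondent characteristics by arm descriptively.
- Name one main arm comparison that is valid under MAR whatever any test shows. It could be the mixed model of section d.2 fitted to all available waves, or IPW or multiple imputation by arm using the earlier anxiety and worry scores.
- Keep complete-case ANCOVA as a sensitivity analysis, and reword the complete-case sentence so that it no longer conflicts with the unbalanced panel.
- Do not describe IPW as correcting non-random loss. A delta-adjusted sensitivity analysis by arm for one-year STAI and Lerman scores would address that possibility.

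The cost is revised wording and modest extra programming. No new data are needed.

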#### d. Multivariate regression analyses

Multivariate regression models will be used to model different patient reported outcomes (PROs) such as comprehension of the information provided, general anxiety or cancer worry, information seeking behaviour, etc. Both cross-sectional and longitudinal models will be estimated.

For all models, a threshold of 5% will be used to assess statistical significance of model parameters.

##### d.1. Cross-sectional models

Logit models will be used to estimate binary dependent variables models. For categorical (ordered) dependent variables, the proportionality of odds-ratio conditions will first be assessed to test the suitability of estimating ordered logit models. If the condition is not verified, multinomial logit models will be estimated. For continuous dependent variables, linear models will be considered. Normality and homoscedasticity of error terms will first be tested before estimation. In case of rejection of normality, generalised linear models (GLMs) will be estimated and in case of rejection of homoscedasticity, heteroscedastic-consistent standard errors will be computed.

Regressors of interests will be selected based on the literature, results of qualitative pre-tests and a priori assumptions. In case many regressors are selected, stepwise selection methods will be considered in order to estimate the most parsimonious model.

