#### Risk perception and behaviour change (Q5) (at baseline, three months, and four years)

As previously underlined, it is essential that all decisions made as part of breast cancer screening are informed and based on sound understanding of good quality information provided. A key element of understanding is how accurately women perceive their own risk of breast cancer following risk-stratified screening, and whether this has been improved, relative to standard screening. For these reasons, we will assess perception of risk of breast cancer, and perceptions of efficacy and risks of different prevention options, to assess the constructs of Protection Motivation Theory, a theory that aims to understand how risk information can translate into behaviour change or not [45]. Uptake of options that may reduce future risk of breast cancer such as increased frequency of mammography in women at high risk, or increases in healthy eating or physical activity, is linked to perceptions of the risk of disease and benefits of these behaviours in reducing risk [11]. By contrast, a potential harm of risk-stratified screening is that those who are told they are low risk may increase their unhealthy behaviours through being falsely reassured (i.e., a certificate of health effect).

To estimate comparative risk and comparative severity scores, participants are asked to choose a category indicating their perceived risk of invasive breast cancer over the next ten years, compared to the population’s average (comparative risk). They are also asked to evaluate, if they were to get breast cancer, how severe they think this would be (comparative severity) on a five-point scale from lower to higher risk.

The behaviour change questions evaluate three different behaviours relating to reducing breast cancer risk: improving diet, increasing physical activity and attending mammography appointments. Five-point scales are used to measure Response Efficacy (the perception of how much the behaviour would reduce the participant’s risk of breast cancer) and Self-Efficacy (how easy or difficult it would be to enact these behaviours). To calculate the intention to change behaviour scores, participants are asked three questions assessing their intention to change the three health-related behaviours on a five-point scale, from “strongly disagree” to “strongly agree” [22].

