#### Trial Programme Satisfaction (Q7) (at one year and four years)

This questionnaire is an evaluation of the overall satisfaction of women with their participation in the study, with the information provided and communication tools used, and with the overall organisation of the trial. The intention to participate in the study is assessed at one year and actualised at four years. Analyses will consider the dropout rate. The questionnaire is an adapted version of a satisfaction questionnaire on organisation of the screening process and the information received, validated by Bairati et al. [29] and currently used in Canada. The questionnaire was modified to integrate specific questions concerning the MyPeBS study. It was validated along with the comprehension and information-seeking behaviour questionnaires, following the same methodology, and consists of seven questions with five-point scale answers.

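### For five-point outcomes, a failed proportional-odds check discards the ordering for every regressor, although relaxing the offending regressor alone would suffice

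*Protocol article*

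**What the plan says.** The rule for ordered outcomes is in Appendix 1, section d.1 (Cross-sectional models). Proportional odds is assessed first and, if it holds, an ordered logit is fitted. Otherwise: "If the condition is not verified, multinomial logit models will be estimated". No intermediate model that keeps the order is named.

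The bivariate rule is in Appendix 1, section c: "For the qualitative or discrete variables, the significant differences between subgroups will be assessed either by means of the Chi-square test or by Fisher's exact". Rank tests appear there only under quantitative variables, as sensitivity analyses when normality fails.

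Several outcomes are ordered five-point answers. For behaviour intention (Q5), "participants are asked three questions assessing their intention to change the three health-related behaviours on a five-point scale". The satisfaction questionnaire (Q7) "consists of seven questions with five-point scale answers". Perceived risk and severity, response efficacy and self-efficacy (Q5) and the five EQ-5D dimensions (Q6) are also on five levels.

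The article does not say whether these items count as discrete, ordered or quantitative. Table 1 in Appendix 2 points Q5 to baseline-adjusted arm comparisons and lists a test of proportions or a Student test for objective 3, which includes quality of life.

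**The concern.** Objectives 3 and 5 ask directional questions about these items: is quality of life better, are women satisfied. Objective 4 asks the same about intentions. An ordered model answers with one arm odds ratio. A multinomial logit on five categories gives four arm coefficients against a reference category, which need not agree in sign. A chi-square test on a two-by-five table gives no direction.

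The switch in d.1 applies to the whole model. If country or another covariate breaks proportionality, the arm effect loses its ordered estimate although arm itself may satisfy the assumption. A check that gains sensitivity as the sample grows will find departures of no practical importance. Items on the same scale could then be reported with different effect measures, according to how each check turned out.

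At stake is mainly whether the arm effects can be read and compared across items. Power is a secondary matter, and it counts in the country-level comparisons that the sample size section says will be well powered.

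**Working it through.** **Inputs from the article**
- Significance level, section c: "The tests will be bilateral with a significance level of 5"%. For regressions, section d: "For all models, a threshold of 5% will be used to assess statistical significance of model parameters".
- Effect and follow-up, Sample size justification: "assuming 70% follow-up of the first 22,000 women, the present study will have over 99% power to detect a very small difference (standard mean difference"; the difference named there is 0.08.
- Allocation, Background: "Participants are randomised 1:1 between the standard arm and the risk-based arm".
- Target: 85,000 women in six countries. No country sizes are given.

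**Step 1. Reproduce the stated power**
- Analysed: 0.70 × 22,000 = 15,400, or 7,700 per arm.
- Noncentrality: λ = 0.08² × 7,700 / 2 = 24.64.
- Power of a two-sided 5% test with 1 df: 99.87%. The article's figure of over 99% is reproduced.

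**Step 2. The same shift tested without order**

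A two-arm comparison of five categories has 4 df. For a pure shift, almost all the information lies in one direction, so λ is taken as unchanged and only the degrees of freedom and the critical value move (3.84 for 1 df, 9.49 for 4 df). At 70% follow-up the full target gives 0.70 × 85,000 = 59,500 analysed, or 29,750 per arm. Country rows are assumptions. Two of them are equal sixths: 15,400/12 = 1,283 and 59,500/12 = 4,958 per arm.

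| Women per arm | λ | 1 df | 4 df | Loss (points) |
|---|---|---|---|---|
| 29,750 (full target) | 95.2 | 100% | 100% | 0 |
| 7,700 (article's example) | 24.64 | 99.9% | 98.8% | 1.0 |
| 4,958 (assumed country) | 15.87 | 97.8% | 90.9% | 6.9 |
| 3,000 (assumed) | 9.60 | 87.3% | 69.6% | 17.7 |
| 2,000 (assumed) | 6.40 | 71.6% | 49.9% | 21.7 |
| 1,283 (assumed country) | 4.11 | 52.7% | 32.8% | 19.8 |
| 1,000 (assumed) | 3.20 | 43.2% | 25.9% | 17.3 |

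The loss cannot exceed 21.8 points at any size; it peaks where the 1-df test has about 69% power.

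Simulation agrees. A standardised difference of 0.08 on the logistic scale is a log odds ratio of 0.08 × π/√3 = 0.145, an odds ratio of 1.156. Over three assumed five-category distributions (4,000 runs each), the rank test had 99.8 to 99.9% and chi-square 98.8 to 99.1% at 7,700 per arm. At 1,283 per arm they had 53 to 55% and 33 to 34%.

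**Step 3. How often might the check in d.1 fail?**

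This assumes that the check is a 5% significance test; the departures are also assumed.
- No departure: about 5%, so the ordered logit is kept about 95% of the time.
- Arm log odds ratios of 0.05, 0.10, 0.15 and 0.20 at the four cut-points, all in one direction: 41% at 7,700 per arm and 96% at 29,750 (3 df).
- Country cut-points scattered with SD 0.05 on the logit scale, six equal countries: about 80% at 15,400 women and about 100% at 59,500 (15 df).

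**Step 4. Would one common odds ratio always be better?**

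Suppose that in the risk-based arm one third of women shift down, one third do not move and one third shift up by the same amount (base probabilities 0.08, 0.17, 0.40, 0.25, 0.10; 7,700 per arm). With shifts of 0.5 on the logit scale, the rank test rejects in 5% of trials, its null level, and chi-square in 35%. With shifts of 0.8 the figures are 5% and 99%. An averaged arm effect can hide opposing movements.

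**The case against.** The strongest reply is that the plan already prefers order. Ordered logit is the first choice, multinomial logit is only the fallback, and proportionality is to be assessed without a stated mechanical cut-off. All of that stands. So does the point that the rejection rates in step 3 rest on departures with no source in the article.

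Chi-square for the five-point items is also an inference. Table 1 calls for baseline-adjusted comparisons of Q5, which chi-square cannot give. The Q5 section speaks of scores, which could lead to ANCOVA. The longitudinal models choose their link by type of outcome and could be ordinal. Assigning each item to a test is often left to a full analysis plan, so the missing assignment alone would not be a finding.

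A reader might infer that the trial gives up about 20 points of power on its ordered outcomes. The documents do not support that. At the article's own effect and interim size the loss is about 1 point, and at the full target none. Losses near 20 points need a setting where the ordered test itself has roughly 50 to 80% power. Nor does step 2 show a loss for the multinomial model under a marked departure, since it assumes a pure shift.

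A reader might also conclude that a common odds ratio should always be the main result. Step 4 shows why not for Q5: the article itself raises false reassurance in low-risk women alongside greater uptake in high-risk women, and these could cancel.

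The written rule in d.1 is untouched by these replies. It discards order for every regressor when a narrower remedy exists.

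**Conclusion.** The point holds as a weakness of model choice and interpretation. The d.1 fallback is broader than the problem it addresses: one non-proportional regressor turns the arm effect into four unordered coefficients. At this sample size that may happen often for trivial reasons, though no rate can be fixed from the article. Section c adds to it by naming only order-ignoring tests for discrete variables, with the class of the five-point items left open.

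The power cost for a pure shift of 0.08 is about 1 point at 7,700 per arm, nil at the full target, and about 7 to 22 points within single countries of about 1,000 to 5,000 women per arm. The country range rests on assumed sizes.

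**What to change.** In d.1, replace the switch to multinomial logit with a partial proportional-odds model that relaxes proportionality only for regressors that clearly violate it.
- If arm is not among them, report a single arm odds ratio.
- If arm is among them, report arm odds ratios at each cut-point.
- For Q5, where opposing shifts could cancel, arm effects may instead be shown by risk group.

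In c, use an ordered test for ordered directional items such as Q7 and the EQ-5D dimensions: a cumulative-logit model with the baseline answer where one is collected, otherwise a Wilcoxon or trend test. Q7 has no baseline measurement. Keep chi-square and multinomial logit for nominal variables, and state which class the five-point items fall in.

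The cost is a change of wording and slightly more modelling work in standard software. Where mild non-proportionality remains, the single odds ratio is an average over cut-points.

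### Stepwise selection in the cross-sectional models, followed by ordinary 5% tests, makes results for null and weak regressors too optimistic

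*Protocol article*

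**What the plan says.** Appendix 1, section d.1 (Cross-sectional models), sets out two stages. The candidates come first from outside the data: "Regressors of interests will be selected based on the literature, results of qualitative pre-tests and a priori assumptions". A second, data-driven stage may follow: "In case many regressors are selected, stepwise selection methods will be considered in order to estimate the most parsimonious model".

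The parent section d (Multivariate regression analyses) gives one rule for inference: "For all models, a threshold of 5% will be used to assess statistical significance of model parameters". That covers a model reached by stepwise selection as well as one fixed in advance.

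The article does not state how many candidates are expected, the direction of the search, the entry or removal criterion, which terms must stay in, or any allowance for selection in the inference. Some of this may stand in a fuller plan, and its absence is not the point here. The point is the combination the article does state.

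Section d.2 (Longitudinal models) does not mention stepwise selection. Section c handles comparisons of quantitative variables by ANCOVA with baseline adjustment, and Appendix 2 describes the arm comparisons for anxiety, cancer worry and risk perception in similar terms.

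**The concern.** Ordinary t-tests and intervals assume that the model was fixed before the outcome was seen. Under stepwise selection a regressor is in the final model because its estimate in these data was large relative to its standard error. A null regressor that survives has been picked for looking non-null. A weak one that survives tends to have been estimated too high. The final-model standard errors take no account of this.

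The results most exposed are associations. The Objectives section wants to know whether comprehension and information seeking go with socio-demographic and socio-economic characteristics, and the Discussion links the findings to recommendations and to access across social groups. The Socio-demographic questionnaire section lists education, profession, income and a deprivation index, which are plausibly correlated. Among correlated candidates, stepwise selection may keep one and drop another largely by chance. A factor chosen on prior grounds can then vanish from the report, while a chance finding appears as a determinant.

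There is also little need for it. The sample sizes in the article can carry 20 or more regressors without strain.

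**Working it through.** **1. The article's own figure.** The Sample size justification works from "assuming 70% follow-up of the first 22,000 women": 22,000 × 0.70 = 15,400, or 7,700 per arm at 1:1 allocation. It claims "over 99% power to detect a very small difference (standard mean difference of 0.08) between the two experimental groups". Check: the standard error of the standardised difference is √(2/7,700) = 0.0161; 0.08/0.0161 = 4.96; power = Φ(4.96 − 1.96) = 0.9987. The claim reproduces and does not depend on stepwise selection. It also supplies the one sample size the article gives for an analysis set, 15,400.

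**2. Assumptions not in the article.** 20 candidate regressors with pairwise correlation 0.3, unit residual variance, backward elimination with removal at p > 0.05, then ordinary 5% tests and 95% intervals on the final model. The comparator is the full 20-regressor model.

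**3. What fixes the size.** With equal correlation ρ and k regressors, the variance inflation is [1 + (k−2)ρ] / {(1−ρ)[1 + (k−1)ρ]} = 6.4/(0.7 × 6.7) = 1.365. The standard error is √(1.365/n): 0.0261 at n = 2,000 and 0.0094 at n = 15,400. The ratio of true effect to standard error (the expected t) drives the distortion.

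**4. Ten weak and ten null regressors (simulation).**

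| n | True effect (SD) | Expected t | Coverage, retained true effects | Estimate / true | ≥1 null kept, stepwise | ≥1 null significant, full model |
|---|---|---|---|---|---|---|
| 2,000 | 0.039 | 1.49 | about 85% | about 1.8 | 54–56% | 38–40% |
| 15,400 | 0.039 | 4.14 | about 96% | 1.00–1.01 | 44% | 41% |
| 15,400 | 0.014 | 1.49 | about 84% | about 1.8 | – | – |

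Full-model coverage is 95%. Rows 1 and 3 share an expected t of 1.49 and show the same distortion. In row 2 the expected t is well above the cut-off of 1.96, and the distortion almost disappears.

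**5. Five true effects among 20, removal at 5%.** Coverage here is over all retained regressors, null ones included.

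- n = 1,000, effect 0.06 SD (expected t 1.62): coverage 62%, overstatement 1.66-fold.
- n = 15,400, effect 0.02 SD (expected t 2.12): coverage 69%, overstatement 1.35-fold.
- n = 15,400, effect 0.06 SD (expected t 6.37): coverage 81%, no overstatement. The shortfall comes from the nulls that stayed in.

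**6. All regressors null, n = 1,000, other removal criteria.** With removal at 5%, every retained interval excludes zero by construction, so coverage is 0%. With removal at 0.157 (what AIC amounts to for a single-parameter term), coverage is 61–63%. With removal at 0.20 it is 70–71%. Across the three criteria, the chance of at least one false positive is 0.40–0.47 with stepwise against 0.37–0.42 in the full model for 10 candidates, and 0.68–0.75 against 0.61–0.64 for 20.

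**7. The randomised comparison.** A null arm term forced into the model (n = 1,000, 20 regressors, correlation 0, removal at 5%) was rejected in 4.2% of runs, so it is not inflated.

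**The case against.** The strongest reply has four parts.

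**Much of the false-positive risk is ordinary multiplicity.** With 20 independent null regressors, 1 − 0.95^20 = 0.64, and the full model has the same 64%. This stands. A reader might take 64% as the price of stepwise selection, but it is not. Likewise, the 54–56% at n = 2,000 means little without its full-model comparator of 38–40%; the excess is roughly 14 to 18 points. The sentence "Adjustments for multiple comparisons (Bonferroni correction) do not appear to be required" does not strengthen the point either. It belongs to the section on bivariate tests and raises a separate question.

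**At the article's sample size the harm is often small.** This stands for effects large enough to be retained almost every time (row 2 of the table). It does not stand for null regressors, for effects near or below the detection limit at that n, or for country and subgroup sets well below 15,400.

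**Stepwise selection is only an option, with no stated criterion.** True: it is conditional on there being many regressors and is merely to be considered. Pruning by p-value is an assumption made here. But looser removal thresholds, including the AIC equivalent, also gave coverage well below 95% for retained nulls. Any rule that uses the outcome to choose terms and then tests them as if fixed has this fault in some degree.

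**The reach is narrow.** This also stands. A reader might infer that the arm comparisons, or objectives 2 to 4 as a whole, rest on stepwise models. The article does not support that. Arm comparisons of quantitative outcomes use ANCOVA. Appendix 2 gives objective 3 tests of proportions, Student tests and correlations, and gives objective 4 arm comparisons and mediation. The longitudinal section does not mention stepwise selection.

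**Conclusion.** The concern holds within limits. The article permits data-driven selection in the cross-sectional models and then applies an ordinary 5% threshold to what remains. For null and weak regressors, the resulting p-values and intervals do not have their nominal properties.

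Under the assumptions listed, retained true effects with an expected t of about 1.5 have roughly 84–85% coverage instead of 95% and are overstated about 1.8-fold. At n = 2,000 that means effects of 0.039 SD; at n = 15,400, effects of 0.014 SD. Effects of 0.039 SD at n = 15,400 are almost undistorted. These figures are illustrations, because the article gives neither the number of candidates, nor their correlation, nor the selection rule. The direction of the error was the same for null and weak regressors under every removal threshold tried.

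The exposure is mainly in the association analyses of comprehension, information seeking and socio-economic characteristics, and grows as country or subgroup sets shrink. The trial's primary endpoint, the stated power, the between-arm ANCOVA and the longitudinal models are not shown to be affected. It is still worth changing, because these associations are meant to inform recommendations and the remedy costs almost nothing.

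**What to change.** Delete the stepwise sentence from section d.1. Base all inference in the cross-sectional models on the full model containing every regressor chosen a priori, and report every coefficient with its interval, whether significant or not. Reporting only the significant rows of a full model would bring the overstatement back. If a shorter model is wanted for presentation, label it descriptive and draw no 5% significance claims from it.

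The cost is a change of wording and longer tables; design and data collection are untouched. The change removes only the distortion that selection adds. Ordinary multiplicity across regressors remains (0.40 for 10 independent nulls and 0.64 for 20), so isolated significant coefficients should still be read with caution.
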